## Abstract

**Background:**

Autism spectrum disorder (ASD) represents a significant public health challenge characterized by persistent social communication deficits and restricted, repetitive patterns of behavior. Current interventions show limited efficacy, particularly for core symptoms. Repetitive transcranial magnetic stimulation (rTMS) and auditory integration training (AIT) have independently demonstrated promise in addressing neurophysiological abnormalities associated with ASD.

**Objective:**

This study aims to evaluate the clinical efficacy of a combined rTMS and AIT intervention compared to rTMS alone and sham stimulation in children with ASD.

**Methods:**

This is a randomized, sham-controlled trial that will recruit 80 children aged 2 to 6 years with a confirmed ASD diagnosis. The randomization of the first 8 participants in this study used a 1:1:1 ratio. To more effectively test the core hypothesis (ie, the efficacy of the combined intervention), greater statistical power will be concentrated on the intervention group (rTMS+AIT), and the randomization ratio was ultimately adjusted to 2:1:1—specifically, (1) rTMS combined with AIT (n=40), (2) rTMS alone (n=20), or (3) sham rTMS (n=20). Primary outcome measures include the Autism Behavior Checklist and Childhood Autism Rating Scale. Secondary outcomes are the Strengths and Difficulties Questionnaire and Repetitive Behavior Scale–Revised. Assessments will be conducted at baseline, an interim time point, and immediately after the intervention. Data will be analyzed using SPSS (version 25.0; IBM Corp).

**Results:**

This study has received funding, with data collection commencing in April 2024. Due to the small initial sample size of 8 participants (5 male and 3 female), no formal statistical comparisons of baseline characteristics between groups have been conducted at this time. It is anticipated that the rTMS combined with AIT intervention will exhibit superior efficacy compared to rTMS only.

**Conclusions:**

This will be the first sham-controlled trial to systematically investigate the potential synergistic effects of a combined rTMS and AIT intervention in children with ASD. The results will provide valuable insights into the neurotherapeutic potential of this combined approach and contribute to the development of evidence-based interventions for ASD.

## Introduction

According to the *Diagnostic and Statistical Manual of Mental Disorders, Fifth Edition*, autism spectrum disorder (ASD) is a complex neurodevelopmental condition characterized by impaired social interaction and communication as well as restricted and repetitive patterns of behavior [1,2]. Individuals with ASD may also exhibit abnormal responses to sensory stimuli, unusual emotional behaviors, difficulties with speech and language comprehension, and challenges with self-care and social adjustment [3]. The prevalence of ASD is a significant public health concern. According to the World Health Organization, approximately 1 in 100 children worldwide is diagnosed with ASD [4]. Data released by the US Centers for Disease Control and Prevention in 2023 showed a sharp increase in the prevalence of autism among children in the United States over the past 20 years [5,6]. Epidemiological survey data from a large sample population in China also indicate a prevalence rate of 0.7% for ASD [7]. Given the growing prevalence of ASD, early assessment, diagnosis, and intervention are crucial. However, the pathogenesis of ASD remains unclear, and there is a lack of specific drug treatments. It is necessary to actively explore effective clinical intervention methods to address this pressing public health challenge.

In recent years, noninvasive brain stimulation, particularly repetitive transcranial magnetic stimulation (rTMS), has been widely applied in the treatment of ASD and has gained recognition among researchers [8,9]. Transcranial magnetic stimulation (TMS) is believed to induce lasting neuroplastic changes in the brain, thereby potentially normalizing social and cognitive functioning in individuals with ASD by stabilizing abnormal neuroplasticity [10]. A meta-analysis by Smith et al [11] of 12 studies demonstrated that TMS improved social withdrawal, repetitive behaviors, and executive function in adolescents with ASD who had an IQ greater than 65, highlighting the significant therapeutic potential of TMS for ASD. Current TMS interventions for ASD primarily target the dorsolateral prefrontal cortex (DLPFC), medial prefrontal cortex, and temporo-parietal junction [12,13]. The DLPFC is involved in multiple higher-order cognitive functions, including emotional regulation, decision-making, attentional control, and adaptive adjustment. In ASD, the core symptoms of repetitive, stereotyped behaviors and social impairments are closely associated with DLPFC dysfunction. Studies using low-frequency rTMS targeting the bilateral DLPFC have demonstrated significant reductions in Repetitive Behavior Scale–Revised (RBS-R) scores following intervention [14,15]. Another study using low-frequency rTMS on the bilateral DLPFC in individuals with ASD showed significant improvements in social behavior after 18 treatment sessions. Similarly, Masuda et al [16] and Casanova et al [17] have indicated that low-frequency rTMS may exert therapeutic effects on social interaction and repetitive behaviors in ASD. In summary, DLPFC dysfunction represents a key neural mechanism underlying the core symptoms of ASD, with particularly pronounced effects on social skills and behavioral regulation. Given its favorable safety profile and emerging evidence of efficacy, rTMS offers a promising intervention for addressing the challenges faced by individuals with ASD.

Studies have shown that most children with ASD experience sensory integration dysfunction [18]. Moreover, the core symptoms of ASD are closely related to abnormal sensory processing, with auditory processing abnormalities being a primary concern [19]. Auditory integration training (AIT), a novel audio therapy initially proposed by French physician Guy Bérard [20], filters out hypersensitive frequencies to reduce auditory cortex sensitivity to sound stimuli, thereby significantly improving auditory attention in children with ASD [21]. Studies indicate that AIT effectively improves language, social interaction, communication, and behavioral skills in children with ASD who also have auditory attention deficits. International studies have explored the physiological effects of AIT on plasma glial cell–derived neurotrophic factor levels. Results demonstrate that AIT significantly elevates plasma glial cell–derived neurotrophic factor levels, thereby improving abnormal sensory processing in affected children [22]. Multiple studies support the efficacy of this method, indicating that when children with ASD can more accurately perceive and process auditory information, their comprehension and expression abilities improve, leading to enhanced functioning in social skills, communication, and related domains [18,23]. However, AIT is considered limited in its capacity to fundamentally activate and repair the nervous system, which may hinder sustained functional recovery [24]. Given this limitation, current research predominantly combines AIT with traditional behavioral training to evaluate treatment outcomes [25,26]. Furthermore, previous studies have often lacked appropriate control groups, necessitating additional research to validate AIT’s efficacy. Nevertheless, AIT can be easily implemented in laboratory or clinic settings, facilitating researchers’ collection of physiological data for objective assessment of treatment outcomes.

Although preliminary findings from these individual interventions are encouraging, the evidence base for their combined application remains limited and is subject to methodological constraints. To our knowledge, the few existing studies on combined rTMS and AIT lack adequate control conditions and are susceptible to placebo effects and observer bias [27,28]. A critical and pervasive limitation in recent studies of noninvasive brain stimulation interventions for ASD is the absence of high-quality sham-controlled trials [29,30]. This significant methodological gap prevents definitive conclusions about the true synergistic efficacy of these combined interventions. Consequently, there is an urgent need for rigorous, well-controlled research evaluating the synergistic effects of these 2 treatment modalities to provide stronger evidence-based support for ASD interventions.

The primary objective of this study is to investigate whether the combination of rTMS and AIT produces superior effects on brain activity and behavior outcomes in children with ASD compared to sham-controlled conditions. We hypothesize that the combined intervention will yield synergistic benefits, and the findings from this study are expected to provide a scientific foundation for optimizing clinical interventions for ASD.

## Methods

### Design and Setting

This is a randomized, parallel-group, sham-controlled trial conducted at the Shenzhen Longgang District Maternal and Child Health Hospital. The flowchart of the experimental design is shown in Figure 1, and the schedule of participant assessments is shown in Table 1. Specifically, participants are randomly assigned in a 2:1:1 ratio to 1 of 3 intervention groups: rTMS combined with AIT, rTMS alone, or sham stimulation. Sham stimulation is used via a “sham coil” with an identical appearance to that of the active TMS coil. Participants, outcome assessors, treating therapists, data analysts, and other study personnel are kept blind to group allocation throughout the trial.

**Figure 1. F1:**
[figure not shown]
Flowchart of the trial. ABC: Autism Behavior Checklist; AIT: auditory integration training; ASD: autism spectrum disorder; CARS: Childhood Autism Rating Scale; RBS-R: Repetitive Behavior Scale–Revised; rTMS: repetitive transcranial magnetic stimulation; SDQ: Strengths and Difficulties Questionnaire.

**Table 1. T1:** Schedule of the participant assessments.

	Study period									
	Baseline (week –1)	Allocation (week 0; T0)	Treatment phase—left DLPFC^a^			Interim time point (T1)	Treatment phase—right DLPFC			Posttreatment time point (week 13; T2)
			Weeks 1-2	Weeks 3-4	Weeks 5-6		Weeks 7-8	Weeks 9-10	Weeks 11-12	
Enrollment										
Eligibility screen	✓									
Informed consent	✓									
Randomization		✓								
Interventions										
rTMS^b^+AIT^c^ group			✓	✓	✓		✓	✓	✓	
rTMS group			✓	✓	✓		✓	✓	✓	
Sham rTMS group			✓	✓	✓		✓	✓	✓	
Assessment										
ABC^d^		✓				✓				✓
CARS^e^		✓				✓				✓
SDQ^f^		✓				✓				✓
RBS-R^g^		✓				✓				✓

a DLPFC: dorsolateral prefrontal cortex.

b rTMS: repetitive transcranial magnetic stimulation.

c AIT: auditory integration training.

d ABC: Autism Behavior Checklist.

e CARS: Childhood Autism Rating Scale.

f SDQ: Strengths and Difficulties Questionnaire.

g RBS-R: Repetitive Behavior Scale–Revised.

### Participants

We are recruiting participants from inpatient and outpatient populations of the Children’s Rehabilitation Department of Shenzhen Longgang District Maternal and Child Health Hospital. Recruitment is being conducted through structured screening procedures. During recruitment, gender is not a restriction. If the proportion is unbalanced, the sample size will need to be increased.

#### Eligibility Criteria

##### Inclusion Criteria

Participants who meet the following criteria are included:

Fulfillment of the diagnostic criteria for ASD according to the *Diagnostic and Statistical Manual of Mental Disorders, Fifth Edition* [31]Age of 2 to 6 years (this age range represents the period of greatest neural plasticity in the developing brain) [32]No significant abnormalities on routine electroencephalography (EEG) examinationNormal olfactory, visual, and auditory function, with no other physical or psychiatric comorbiditiesLegal guardian being informed of the study procedures and providing written informed consent

##### Exclusion Criteria

Participants who meet any of the following criteria are excluded:

Significant abnormalities on cranial magnetic resonance imaging or severe cardiopulmonary insufficiencyChildren with schizophrenia, epilepsy, deafness, metabolic diseases, or other mental conditionsUse of psychotropic medications or nutritional supplements for symptom management within the previous 3 monthsHearing impairments or abnormalitiesPresence of intracranial or peristimulation metallic foreign bodies, cardiac pacemakers, or other implanted electronic devicesPrevious receipt of ASD-specific interventions or comprehensive rehabilitation training

### Sample Size

Sample size calculation was based on one-way ANOVA comparing the primary outcome measure (Autism Behavior Checklist [ABC] scores) among the 3 groups. The calculation was performed using the PASS software (version 15; NCSS, LLC) with the following parameters: significance level of α=.05 (2 sided), statistical power of 1 – β = 0.90, and number of groups of *k*=3. On the basis of previous similar studies [33,34], the within-group SD is set at σ=6.5, yielding a medium to large effect size (Cohen *f*). The calculation indicated that a minimum sample size of 15 participants per group was required. Accounting for an anticipated dropout rate of approximately 20%, a total of 20 participants will be recruited for each group. The following standard ANOVA sample size formula was applied: n = ψ^2^ × (σ^2^) / (*k* × *d*^2^).

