## Results

### Overview

This study commenced data collection in April 2024. It is anticipated that the rTMS combined with AIT intervention will exhibit superior efficacy compared to rTMS only.

Currently, 8 participants (5 male and 3 female) have been recruited and randomized. Due to the limited sample size, this study has not yet conducted statistical comparisons of baseline characteristics among the 3 groups. The pooled baseline characteristics of the enrolled participants are as follows: mean age of 4.12 years, mean total ABC score of 53.38, and mean total Childhood Autism Rating Scale (CARS) score of 35.25. Recruitment and follow-up of all participants are ongoing.

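### The sample-size statement does not fit together: 15 per group gives 90% power only at a Cohen f of about 0.55, not a medium-to-large effect, and the calculation was not redone for 40/20/20

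*Protocol article*

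**What the plan says.** The Sample Size section of the Protocol article sets out the calculation. "Sample size calculation was based on one-way ANOVA comparing the primary outcome measure", the ABC score, among three groups. The significance level is 5%, with "statistical power of 1 – β = 0.90", and the software named is PASS.

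On the effect size, the section cites two earlier studies and says that "the within-group SD is set at σ=6.5, yielding a medium to large effect size" on Cohen's f scale. The result is: "The calculation indicated that a minimum sample size of 15 participants per group was required". After an allowance of about 20% for dropout, "a total of 20 participants will be recruited for each group".

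The section then prints n = ψ² × σ² / (k × d²) as the formula used. Neither ψ nor d is defined or given a value.

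Elsewhere the design is different. The abstract's Methods paragraph says that the trial "will recruit 80 children aged 2 to 6 years", split 40/20/20. The Design and Setting and Protocol Amendment sections confirm a 2:1:1 ratio, adopted after the first 8 children had been randomized 1:1:1. The stated reason is to gain power for the combined arm, but no power figure accompanies the change.

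**The concern.** For a one-way ANOVA, the number of groups, the significance level, the power and Cohen's f together fix the group size. The section gives all but f as numbers, and f as a verbal class. Fifteen per group looks far too few for that class at 90% power. The sentence on the SD also cannot be right as written: f is the spread of the group means divided by the within-group SD, so an SD without means yields no f.

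This section is the trial's only justification of its size. If the 90% is taken at face value, a null result would be read as good evidence against a medium-to-large effect, when the design could easily miss one. The calculation also describes a trial of 60 in equal groups, which is no longer being run. No power is stated for combined versus sham or combined versus rTMS alone, the comparisons that the Objective, Results and Discussion point to.

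**Working it through.** **Inputs from the Sample Size section:** k = 3, α = 0.05, power 0.90, σ = 6.5, n = 15 per group, dropout about 20%.

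**Assumption:** medium and large mean Cohen's conventional f = 0.25 and f = 0.40. The document prints no number.

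**1. Trying to reproduce 15.** This cannot be done from the printed inputs, because f is missing. The question can be turned round: what f makes 15 correct? Overall power is the probability that a noncentral F, with k − 1 and N − k degrees of freedom and noncentrality λ = N f², exceeds the 5% critical value. Here N = 45, the degrees of freedom are 2 and 42, and the critical value is 3.22.

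| f | λ = 45 f² | Power, 15 per group | n per group for 90% |
|---|---|---|---|
| 0.25 | 2.81 | 28.5% | 69 |
| 0.325 | 4.75 | 45.4% | 41 |
| 0.40 | 7.20 | 63.5% | 28 |
| 0.50 | 11.25 | 83.4% | 18 |
| 0.55 | 13.61 | 90.0% | 15 |

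Fifteen is the minimum for f from about 0.55 to 0.57. Relaxing α to 0.10 does not rescue the label: power is then 41% at f = 0.25 and 75% at f = 0.40.

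**2. What f = 0.55 means in ABC points.** The SD of the means is 0.55 × 6.5 = 3.57.
- If one group differs from two equal groups, the difference is 3.57 × 3/√2 = 7.6 points.
- If the three means are evenly spaced, the range is 3.57 × √6 = 8.8 points.

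**3. The dropout step.** 15/0.80 = 18.75, so 19. Rounding to 20 is fine.

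**4. The printed formula.** Suppose ψ² is λ/(k − 1), with the large-sample λ = 12.65, so ψ² = 6.33, and d is the SD of the group means. Then n = 6.33/(3 f²), which is 15.0 at f = 0.375. With ψ of about 2.61 it gives 14.2, rounded up to 15, at f = 0.40. The exact test needs 32 and 28 per group at these values. On this reading the formula lacks a factor k − 1 = 2, but the reading is an assumption.

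**5. The design now in force.** A 20% loss from 40/20/20 leaves 32/16/16. With unequal arms, power depends on which arm differs. Here f is the unweighted SD of the three means over σ, and λ = Σ nᵢ(μᵢ − μ̄)²/σ², with μ̄ the size-weighted mean.

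| Pattern of means | λ at f = 0.25 / 0.40 | Power |
|---|---|---|
| Combined arm alone differs | 4.50 / 11.52 | 44% / 85% |
| Evenly spaced, combined arm extreme | 4.13 / 10.56 | 41% / 82% |
| One 16-child arm alone differs | 3.38 / 8.64 | 34% / 73% |
| Evenly spaced, combined arm in the middle | 3.00 / 7.68 | 31% / 68% |

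If f is weighted by group size instead, λ = 64 f² and power is 40% / 80%; without any loss (40/20/20) it is 49% / 89%.

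**6. The key contrasts.** For combined versus sham, or combined versus rTMS alone, a two-sided t test with 32 versus 16 has 46 degrees of freedom and noncentrality δ/√(1/32 + 1/16) = δ/0.306, where δ is the difference in SDs. Unadjusted for testing two contrasts, 90% power needs δ = 1.01 (1.01 × 6.5 = 6.6 points) and 80% needs δ = 0.88 (0.88 × 6.5 = 5.7 points).

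**The case against.** The strongest reply is that 15 has not been shown to be wrong. The section says that PASS was run on inputs drawn from two earlier studies, and neither those studies nor the PASS output is shown. If f of about 0.55 was entered, 15 per group is correct and only the verbal label is loose. The range 0.25 to 0.40 is a convention brought to the document, not a number in it. This stands, and it limits the finding to an inconsistency. It does not remove it: the section names both the index (Cohen's f) and the class, and even the conventional large value leaves power under 64%.

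A reader might infer that a missing k − 1 factor produced the 15. The documents do not support that. With ψ and d undefined, two different effect sizes can each be made to return 15, and the number may have come from PASS rather than the formula.

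A reader might also take 28% to 64% as the power of the trial. That range belongs to 45 evaluable children in equal groups. The trial recruits 80, and the figures for 32/16/16 are higher.

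**Conclusion.** The point holds as an internal inconsistency. Under the conventional benchmarks, 15 per group, 90% power and a medium-to-large f cannot all be true. Either the label is wrong, because f of about 0.55 lies above the conventional large value, or the size and power statement is wrong, because power is about 28% to 64% at f = 0.25 to 0.40. The document does not allow a choice between the two. The mismatch between 20 per group (60 in all) and 40/20/20 (80 in all) needs no assumption.

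For the actual design, the overall test has about 31% to 44% power at f = 0.25 and 68% to 85% at f = 0.40. These figures assume exact F-test power, a common SD, 20% loss in each arm, and the four patterns of means shown.

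A reader might go further and infer from the "mean total ABC score of 53.38" that an SD of 6.5 is too small, since few children would then reach the ABC diagnostic score of 67. The documents do not support this. The mean comes from 8 children, eligibility rests on DSM-5 criteria with no ABC threshold, and the section does not say whether 6.5 refers to baseline, posttreatment or change scores.

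**What to change.** Revise the Sample Size section as follows.

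- State the value of f, or the ABC group means or differences, actually entered in PASS.
- Make the label and the power agree. If 15 per group at 90% stands, replace the verbal class with the number (about 0.55). If a medium-to-large effect was meant, restate the power.
- Define ψ and d and correct the formula, or remove it.
- Replace 20 per group with 40/20/20, and 32/16/16 after 20% loss.
- State the overall power for that design with the assumed pattern of means, and the detectable difference for combined versus sham and combined versus rTMS alone: about 1.01 SD at 90% and 0.88 SD at 80%, unadjusted.

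This changes wording only and adds no children. The cost is that the stated power becomes less favourable. The study timeline lists end-point assessment and analysis as future work, so the correction can be made before the results are read.

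### The Sample Size section still recruits 20 per group (60, equal arms) while the Abstract recruits 80 as 40/20/20, so the stated power belongs to a design that is not being randomised

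*Protocol article*

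**What the plan says.** The Sample Size section is current Methods text and gives one calculation: "Sample size calculation was based on one-way ANOVA comparing the primary outcome measure" (the ABC score) among the three groups, with "significance level of α=.05 (2 sided"), "statistical power of 1 – β = 0.90", "number of groups of *k*=3" and "the within-group SD is set at σ=6.5". It reports a minimum of 15 per group, allows for about 20% dropout, and concludes that "a total of 20 participants will be recruited for each group".

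The Abstract (Methods) gives a total of 80 and lists the arms as "1) rTMS combined with AIT (n=40), (2) rTMS alone (n=20), or (3) sham rTMS (n=20"). Design and Setting says that "participants are randomly assigned in a 2:1:1 ratio to 1 of 3 intervention groups", without a total or arm sizes. Protocol Amendment and Table 2 say that the first 8 children were randomised 1:1:1 and that the ratio then became 2:1:1, to put more power on the combined arm. Neither gives a new sample size. Participants adds that the sample size will have to rise if the gender proportion is unbalanced, and sets no limit.

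**The concern.** Equal arms of 20 and a 2:1:1 allocation cannot both describe the same trial. The two control arms agree at 20 each; the combined arm does not. The ratio was changed for reasons of power, yet the only power statement in the article was derived for equal arms, so a reader cannot tell what power or detectable difference goes with 40/20/20. A planned sample size is also the figure against which the final report will be checked. It should be a single number, and it should come from the design in use.

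**Working it through.** **Inputs.** From Sample Size: three groups, alpha 0.05 two-sided, power 0.90, SD 6.5, 15 evaluable per group, about 20% dropout. From the Abstract: 80 in total, 40/20/20. From Protocol Amendment: 8 children at 1:1:1, then 2:1:1.

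**1. The plan's own figure.** Dropout step: 15 / (1 − 0.20) = 18.75, so 19, which the plan rounds to 20. Total: 3 × 20 = 60. This step reproduces, and it leads to equal arms. The ANOVA step cannot be rerun forward, because the effect is given neither as a number nor as group means. Solved backwards (noncentral F), 15 per group at 90% power needs Cohen f = 0.55.

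**2. The other total.** 40 + 20 + 20 = 80. The difference is 80 − 60 = 20 children, and 40 − 20 = 20 of them are in the combined arm. The inputs shown do not lead to 40 or 80.

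**3. Does 40/20/20 meet the plan's minimum?** 0.8 × 40 = 32 and 0.8 × 20 = 16, so 32/16/16 evaluable. Every arm is above 15. Using the solved f = 0.55 and the group means it implies, omnibus ANOVA power is 92.0% at 16/16/16. At 32/16/16 it is 95.1% to 98.8%, depending on which arm differs.

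**4. Detectable difference, combined versus one comparator.** Two-sample noncentral t, two-sided 0.05, 90% power, SD 6.5:

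| Evaluable | √(1/n₁ + 1/n₂) | Detectable d | ABC points (d × 6.5) |
|---|---|---|---|
| 16 vs 16 (Sample Size section) | 0.354 | 1.185 | 7.70 |
| 32 vs 16 (Abstract) | 0.306 | 1.014 | 6.59 |

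**5. What the randomisation sequence gives.** With 8 at 1:1:1 and 72 at 2:1:1, the expected arms are 8/3 + 72/2 = 38.7 and 8/3 + 72/4 = 20.7, so 38.7/20.7/20.7. Less 20%, that is 30.9/16.5/16.5. The standard-error factor for combined versus one comparator is then √(1/30.9 + 1/16.5) = 0.305, against 0.306 in the table, so the detectable difference is again about 6.6 points. The departure from 40/20/20 is about one child per arm and has no practical effect on power, but the arm targets printed should sum to the total.

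**6. Could 60 be reached under 2:1:1?** With 8 at 1:1:1 and 52 at 2:1:1, the expected arms are 8/3 + 52/2 = 28.7 and 8/3 + 52/4 = 15.7. Both control arms fall short of 20.

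**The case against.** The strongest defence is that the document resolves itself. The Abstract says that the ratio was adjusted and gives the resulting arms, Design and Setting and Protocol Amendment agree on 2:1:1, and 20 in each control arm at 2:1:1 implies about 40 in the combined arm. On that reading the Sample Size sentence is a remnant of the 1:1:1 plan. This is the likely explanation and it stands, but it explains the mismatch without removing it.

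Three stronger readings are tempting and are not supported:

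- **That the trial is underpowered.** It is not, on the plan's own terms. Step 3 shows every arm above the minimum of 15, with omnibus power no lower than in the 60-child plan.
- **That stopping at 60 or at 80 could each be called per protocol.** Under the ratio now in force, a stop at 60 gives about 28.7/15.7/15.7 (step 6), which meets neither the 20 per group of Sample Size nor the 40/20/20 of the Abstract.
- **That no recalculation was ever made.** The article condenses a full protocol that is not shown, and a recalculation may be there. What can be said is that the section printed here was not brought into line.

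It is also fair to note that 80 and 40/20/20 stand in the Abstract only, that the pairwise comparison in step 4 is not the ANOVA on which the plan was sized, and that its 16 versus 16 row describes a design no longer being randomised.

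**Conclusion.** The inconsistency is real and should be corrected. Sample Size plans 60 children in equal arms; the Abstract plans 80 as 40/20/20 and the trial randomises 2:1:1. The printed 90% power and 15-per-group minimum belong to the equal-arm design. The size is 20 children, all in the combined arm, and roughly 7.7 against 6.6 ABC points detectable at 90% power for combined versus one comparator. The larger design is the more sensitive one, so the fault lies in the statement of the sample size and not in the adequacy of the numbers. The detectable differences rest on the plan's SD of 6.5 and 20% dropout. The omnibus powers also rest on f = 0.55, which was solved from the plan's figures and is not given there.

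**What to change.** - In Sample Size, replace the 20-per-group sentence with one total and arm targets that sum to it and agree with the Abstract. Either keep 40/20/20 and set the remaining 72 allocations to reach it given how the first 8 fell, or state the expected 38.7/20.7/20.7 and edit the Abstract to match.
- Restate power or detectable difference for that unequal design at the matching evaluable numbers: 32/16/16 for the first option, about 30.9/16.5/16.5 for the second. With SD 6.5, both give about 6.6 ABC points at 90% power for combined versus one comparator. Label the figure as re-derived after the ratio change.
- Reconcile the total with the clause in Participants that the sample size will need to increase if the gender proportion is unbalanced, so that the document has one rule for when recruitment ends.

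The cost is wording and one recalculation, with no added children or procedures for the restatement itself. The stated power or detectable difference will change. Results reports 8 children randomised and recruitment ongoing.
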